## Methods

### Study design

This is a single-arm, non-randomised feasibility study using a pre-post evaluation design. Any medication changes related to PIM and other medication issues before and after medication review will be compared. An explanatory sequential mixed method approach will be used for data collection and analysis, where the qualitative findings (e.g., interviews) will be used to explain the quantitative findings (e.g., recruitment rate, implementer survey results) [29]. This study consists of two parts: (1) implementation phase of the intervention (6 months) and an (2) evaluation phase (3 months). An outline of the feasibility study including the intervention and evaluation phases is shown in Fig. 1. Ethics approval was obtained from National Healthcare Group Domain Specific Review Board (NHG DSRB) domain F (Ref. no: 2022/00491). The reporting of this protocol is guided by the standard protocol items: recommendations for interventional trials (SPIRIT) [30] (see Additional file 1: SPIRIT 2013 checklist). The Clinical Trial registration for this study is NCT05756478.

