### Screening and recruitment of patients

Eligible patients will be pre-screened and invited to join the study by their attending GRM physicians through convenience sampling. The inclusion criteria are as follow: aged 65 and above, current patient of GRM outpatient clinic, and taking five or more medications daily. On the other hand, patients will be excluded if they are below 65 years old, currently receiving other types of pharmacist services (e.g., medication therapy management), are unable to understand and communicate in English, Chinese, or Malay and if patient or caregiver decline to participate in the study. Participation in this study is fully voluntary, and if they agree to participate, written informed consent will be taken face-to-face by a study team member at each hospital. There is no consensus on the optimal sample size for pilot or feasibility studies and the size is dependent on the objective of the study [33]. Hence, we did not perform a sample size calculation. Instead, we consulted and discussed with stakeholders at both sites and agreed to recruit 30 patients per site for this study, which will provide sufficient insights into the implementation process.

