### Intervention specification

The prototype for the intervention evolved from multiple scoping reviews and modified Delphi studies and was finalised through a co-creation exercise with stakeholders consisting of geriatricians and pharmacists at both study sites during phase 1. In summary, various theoretical frameworks and taxonomy, such as Theoretical Domains Framework (TDF), Behaviour Change Wheel (BCW), and Behaviour Change Techniques (BCTs), were employed at different time points to develop the intervention [34–36]. The detailed account of the intervention development process has been reported in another publication [23]. The main components for this intervention are: (1) pharmacist-facilitated medication review with feedback and recommendation to physicians and (2) physicians communicating medication changes made by other prescribers when needed. Table 1 shows the process of operationalisation of the BCTs in the Pro-M study.

**Table 1 Tab1:** Operationalisation of BCTs in Pro-M study

BCTs identified from modified Delphi study [37]	Context during phase 1 prototype development	Operationalizing BCTs in the Pro-M Study
Credible source	Pharmacists who are experienced in geriatric pharmacology	Medication reviews are led by pharmacists, who will be present at the clinic during review sessions
Restructuring the physical environment	Presence of pharmacist in clinics	
Instruction on how to perform the behaviour	Guidelines to assist in optimizing prescribing	Pharmacists will conduct medication review using prescribing tools (e.g., Beers Criteria)
Information about health consequences	Feedback from pharmacists on occurrence of PIMs post-medication review	Physicians will receive patient-specific feedback on PIMs or other medication issues identified by pharmacists
Feedback on outcomes of behaviour		
Problem solving	Physicians will identify medication problems and/or discrepancies, and then discussing with pharmacists as well as patients for necessary changes to be made	Physicians will ascertain medication review outcomes and any recommendations from the pharmacists, before making the next prescribing decision (e.g., to reduce PIMs)
Goal setting (outcome)		
Goal setting (outcome)	Ensuring proper documentation on reasons behind addition or removal of medications and provide feedback to other relevant prescribers	Documentation of medication indications and communicating changes to other relevant prescribers
Feedback on outcomes of behaviour		

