#### Secondary outcomes and data collection

To provide information for sample size calculation for the next phase scale-up study, the average number of PIMs per patient before and after medication review and the prevalence of PIMs among patients will be collected. For the purpose of this study, prevalence is defined as having at least one PIM prescribed. Medication data on identified PIM and other medication issues will be collected over two time points: once during the medication review and a retrospective data collection from patient’s last GRM appointment. The retrospective data will form the comparison and represent ‘usual care’ where medication review is only done in an ad-hoc and informal basis, if any. This comparison will help to ascertain if medication reviews impact physicians’ prescribing decisions in any way.

In addition, a basic cost analysis will be conducted to compare the cost of manpower for medication review and the cost of PIMs or other medications issues identified before and after the medication reviews. Manpower cost to conduct medication reviews will be estimated by the time needed to a conduct a medication review. Cost of PIMs and other medication issues identified and resolved will be collected to estimate the monthly cost savings from discontinued medications and any substituted medications, if there are [21]. The unit cost of medications will be calculated using the private costs of medications before government subsidies. The cost information collected will provide insights on the longer-term sustainability of implementing medication review in routine care for older adults with multimorbidity.

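### The usual-care comparator visit has no date limit, so for some later recruits it may fall inside the six-month implementation phase and carry indirect influence from the intervention (minor)

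*Protocol article*

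**What the plan says.** All references are to the Protocol article.

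- **Comparator.** Secondary outcomes and data collection sets two time points for the medication data: "once during the medication review and a retrospective data collection from patient’s last GRM appointment". It then says: "The retrospective data will form the comparison and represent" usual care, which it describes as a setting "where medication review is only done in an ad-hoc and informal basis, if any". The earlier appointment is given no date limit.
- **Phase length.** Study design sets out an "implementation phase of the intervention (6 months) and an (2) evaluation phase (3 months").
- **Who is enrolled.** Screening and recruitment of patients requires a "current patient of GRM outpatient clinic, and taking five or more medications daily". The sites "agreed to recruit 30 patients per site for this study", so 60 in all.
- **Who receives the intervention.** Attending clinic physicians invite and refer patients (Setting; Screening and recruitment of patients). In Table 1 of Intervention specification, "Physicians will receive patient-specific feedback on PIMs or other medication issues identified by pharmacists", and the pharmacists are in the clinic during review sessions. Each consenting patient has a single review.
- **Use of the result.** The pre-post comparison is meant to show whether reviews affect prescribing. Under Quantitative data, a paired t-test on PIMs before and after review is offered as a source for the scale-up effect size.

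**The concern.** The comparator is tied to each patient's own visit calendar, while the intervention starts at a site on a calendar date. For the first recruits, the previous appointment necessarily precedes that start. For a patient recruited late in the phase it may not. By then the same physician may have had pharmacist feedback on several other patients and worked with a pharmacist in the clinic. Table 1 builds the intervention from behaviour change techniques aimed at prescribing, so some carry-over to a physician's other patients is plausible.

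If that happens, the pre value for those patients is already somewhat improved and the pre-post difference shrinks. Obtaining this difference for the scale-up sample size is a stated secondary aim. The limitations in the Discussion cover small numbers and convenience sampling. Carry-over is a question of bias rather than precision, so the caveat about power does not cover it.

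**Working it through.** The article states no sample size calculation or effect size, so there is no figure to reproduce. Two things can be checked: whether overlap is possible, and whether its effect can be sized.

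**1. Is overlap possible?**

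From the article: phase length 6 months; 60 patients. Assumed, because the article is silent: even recruitment over the phase, and a fixed interval of g months between comparator visit and review.

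Share of comparator visits inside the phase = max(0, (6 − g)/6).

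| Assumed interval g (months) | Share inside the phase | Patients of 60 |
|---|---|---|
| 2 | 4/6 = 67% | 40 |
| 3 | 3/6 = 50% | 30 |
| 4 | 2/6 = 33% | 20 |
| 5 | 1/6 = 17% | 10 |
| 6 or more | 0% | 0 |

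Overlap is therefore possible under the rule as written, but only with intervals under six months.

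**2. Can the effect be sized?**

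Let c be the share of the intervention effect that carries over to other patients of the same physicians. No value for c can be taken from the article. Take g = 3 and two assumed patterns:

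- *Full carry-over from the first day:* understatement = 0.5 × c.
- *Carry-over rising linearly to c at month 6:* in-phase comparator visits fall in months 0 to 3, on average at month 1.5, so average carry-over is (1.5/6) × c = 0.25c. Understatement = 0.5 × 0.25 × c = 0.125c.

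If the standard deviation of the differences is unchanged, a scale-up study sized on the reduced difference is larger than needed by the factor 1/(1 − understatement)².

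| Assumed c | Full from first day | Sample size factor | Linear rise | Sample size factor |
|---|---|---|---|---|
| 0.10 | 5.0% | 1.11 | 1.25% | 1.03 |
| 0.25 | 12.5% | 1.31 | 3.1% | 1.07 |
| 0.50 | 25.0% | 1.78 | 6.25% | 1.14 |

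At g of 6 or more every entry is zero. At one and the same interval the answer runs from about 1% to 25%, depending wholly on two choices the article does not inform. The table shows that the size cannot be determined; it is not an estimate.

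**3. How much exposure would there be?**

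With even recruitment, 30/6 = 5 reviews take place per site per month. By month 1.5, the average time of the in-phase comparator visits when g = 3, about 1.5 × 5 = 7.5 reviews have been done at a site, spread over however many physicians refer.

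**The case against.** The strongest reply is that the usual-care label meets the article's own definition. Usual care is described there by the absence of formal medication review. Since each patient is reviewed once, no comparator visit can contain that patient's study review. This stands. A reader might infer that a visit inside the phase is simply not usual care, but that needs a stricter definition, free of any physician learning, which the article does not adopt.

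Second, carry-over is conjecture. The feedback is specific to the patient reviewed, exposure is thin, and nothing in the article reports or assumes learning across patients. This also stands, and it limits the point to a possibility.

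Third, the outcome is secondary, the Discussion disclaims effectiveness, and the likely error is conservative: it would make the scale-up study larger, not underpowered. This lowers the severity. It does not remove the point, because the difference is still offered as an effect size.

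Fourth, visit dates and sensitivity analyses are details that an article commonly leaves to a fuller document. That is fair for the extraction form, and the date may already be collected. The article does, however, define the comparator and say what it represents, and that definition is what leaves the overlap open.

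A reader might also conclude that the comparator should be moved to the last visit before site start. The documents do not make that clearly better. It would skip intervening visits, and ordinary prescribing changes made there would be credited to the review. The nearest earlier visit limits that drift.

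**Conclusion.** The point holds as a minor one. The article labels each patient's last appointment as usual care without relating it to the start of implementation. If visit intervals are under six months, some later recruits' comparator visits may follow the start of pharmacist feedback to their physicians about other patients. Any influence would be indirect and would probably understate the pre-post PIM change.

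A reader might infer a definite loss, such as a quarter of the effect. The documents do not support that or any other percentage: the visit interval, the recruitment pattern and the degree and timing of carry-over are all absent. With intervals of six months or more the issue vanishes. The primary feasibility outcomes do not depend on this comparison.

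**What to change.** Keep the last appointment as the main comparator. Extract its date with the medication data and record each site's implementation start date. Add a sensitivity analysis of the paired PIM difference restricted to patients whose comparator visit precedes their site's start, and report both estimates when deriving the scale-up effect size.

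The cost is one extra field in a chart extraction that is already planned, plus one repeat analysis. The downside is precision. If 30 of 60 patients remained, as with an assumed three-month interval, the standard error would be about √(60/30) = 1.41 times as large, given the same standard deviation. The restricted group would also lean towards early recruits and patients seen less often, so a gap between the two estimates would be a signal to consider and not proof of carry-over.

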The resulting intervention, Pro-M or Appropriate Prescribing for older adults with Multimorbidity, is a physician-pharmacist collaborative care intervention to optimise prescribing for older adults with multimorbidity at outpatient specialist clinics in Singapore’s public hospitals. The main component is a pharmacist-facilitated medication review, with physicians communicating changes to other relevant prescribers. This second phase study aims to evaluate the feasibility of the intervention from the perspectives of the physicians and pharmacists involved in the implementation. The rationale of conducting a feasibility study is to test and evaluate the implementation of the intervention in real-world settings and identify potential implementation challenges that need to be addressed and adapted for the full-scale study in order to reduce potential resource wastage [24, 25]. As the intervention was co-created with stakeholders from the two study sites, our conjecture is that the implementation of the intervention would likely be feasible to the physicians and pharmacist. In addition, our study aims to provide quality care to the older population in Singapore, which aligns with the Singapore’s Voluntary National Review [26] which takes guidance from United Nations’ Sustainable Development Goals (SDGs) [27] on the goal of good health and well-being.

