### Study aims and objectives

The aims of the study are:

To assess feasibility of the intervention among stakeholders using Proctor’s implementation outcomes [28]: Appropriateness, Penetration, Acceptability, Fidelity, Feasibility, and Sustainability (primary).To collect data on recruitment rate for sample size calculation in the next phase scale-up study (secondary).To collect pre-post data on the prevalence of PIMs and/or other medication issues for sample size calculation in the next phase scale-up study (secondary).To conduct a cost analysis of the intervention based on manpower cost and the cost of PIMs and/or medications with other issues identified before and after the medication reviews (secondary).

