### Outcome measures

#### Primary outcome and data collection

The primary focus of this study is to assess the feasibility of implementing the physician-pharmacist collaborative care intervention from the stakeholders’ perspectives, which will be reported qualitatively. Surveys will be conducted to explore stakeholders’ attitudes and experiences during the intervention. In-depth interviews will follow with selected implementers to elicit insights as well as qualitative interpretations to the survey findings.

A short 11-item patient survey (see Additional file 2: Pro-M patient survey) will be administered after the intervention to measure patients’ attitudes toward acceptance and appropriateness of the intervention. They will also be asked if they will be willing to pay for medication review as part of their routine care in the future. On the other hand, physicians and pharmacists involved in the intervention will be invited to participate in the evaluation phase. To achieve this goal, a 25-item implementer survey was developed using Proctor’s implementation framework (Penetration, Appropriateness, Acceptability, Fidelity, Feasibility, and Sustainability) [28] and each item will be measured using a 5-point Likert scale (see Additional file 3: Pro-M implementer survey).

In addition, some quantitative data, such as time taken to conduct the medication review, number of discussions between physicians and pharmacists, number of communication efforts by the physicians, and the number of agreements between the physicians and the pharmacists on PIM and other medication issues identified, will be collected alongside the intervention. This quantitative information will be triangulated with the survey and interview results to provide a fuller picture on the feasibility of the intervention.

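### The cost analysis is meant to cost the intervention, but manpower is priced on medication-review time only, so physician communication with other prescribers carries no cost

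*Protocol article*

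**What the plan says.** Under Study aims and objectives, the last secondary aim is "To conduct a cost analysis of the intervention based on manpower cost and the cost of PIMs and/or medications with other issues" found before and after the reviews. The object being costed is the intervention.

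The intervention has two main components. Intervention specification gives the first as "1) pharmacist-facilitated medication review with feedback and recommendation to physicians" and the second as physicians' communication about medication changes, to be done as required. The Introduction describes the same pair: a pharmacist-facilitated review, "with physicians communicating changes to other relevant prescribers".

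Secondary outcomes and data collection sets the costing. The plan there is that "a basic cost analysis will be conducted to compare the cost of manpower for medication review and the cost of PIMs" or other medication issues. The manpower input is defined in one sentence: "Manpower cost to conduct medication reviews will be estimated by the time needed" for the review. No other staff time is named as an input.

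Primary outcome and data collection lists the process data. It names time for the medication review. The other staff activities appear as counts: "number of discussions between physicians and pharmacists, number of communication efforts by the physicians". The stated use of these data is triangulation with the survey and interview results on feasibility. They are not linked to the cost analysis.

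**The concern.** The aim and the costing rule cover different things. A cost analysis of the intervention should price the staff time that the intervention adds. The rule prices the review and leaves the physicians' communication with other prescribers unpriced, although the article presents that communication as a main component.

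This matters because the article intends the cost result to inform whether the service can be sustained in routine care, and the Discussion lists the cost analysis among the data that will shape the scale-up study. The Introduction also gives coordination, alongside time, as a reason why such reviews are not routine in outpatient clinics. A manpower figure that prices the review but not the coordination would omit one of the two burdens that the article itself names. Anyone who carried that figure into scale-up planning as the cost of the intervention would be working with a number that is too low.

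**Working it through.** The article states no cost, wage or duration, so there is no figure to reproduce. The check sets each staff activity against the costing rule.

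| Activity | Where described | Data named | In the costing rule? |
|---|---|---|---|
| Pharmacist's medication review | Intervention specification, component 1 | Time | Yes |
| Feedback to and discussion with the physician | Part of component 1; discussions also listed separately under Primary outcome and data collection | Number of discussions | Unclear: depends on what review time includes |
| Physician's communication with other prescribers | Introduction; Intervention specification, component 2 | Number of efforts | No |
| Documentation of changes | Intervention specification | None named | No |

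**Cost identity.** Let

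- R = review time × pharmacist rate
- D = discussion time not already in R, for both staff, each at their own rate
- C = physician documentation and communication time × physician rate

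with D and C limited to time beyond usual care. Then

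full manpower cost = R + D + C

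planned manpower cost = R

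understatement = D + C; omitted share = (D + C) / (R + D + C)

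If D + C is above zero, the planned figure is too low. The documents supply neither D nor C.

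**Illustration. Every number here is an assumption and none comes from the article.** Take a 30-minute review at relative rate 1, so R = 30, and a physician rate of 2.

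- *Communication only (discussion already in review time).* With 5 to 10 physician minutes per patient, C = 5 × 2 = 10 to 10 × 2 = 20. Full cost relative to planned: (30 + 10)/30 = 1.33 to (30 + 20)/30 = 1.67.
- *Discussion also left out.* With 5 to 15 minutes for both staff, D = 5 × (2 + 1) = 15 to 15 × (2 + 1) = 45. Then D + C = 25 to 65, and the ratio is (30 + 25)/30 = 1.83 to (30 + 65)/30 = 3.17.
- *A different set of assumptions:* 5 to 15 extra physician minutes at 1.5 to 3 times the pharmacist rate. The omitted amount is 5 × 1.5 = 7.5 to 15 × 3 = 45. The omitted share is 7.5/37.5 = 20% to 45/75 = 60%, a ratio of 37.5/30 = 1.25 to 75/30 = 2.5.
- *Lower limit.* All of these charge the extra time to every patient and treat all of it as additional to usual care. If communication is seldom needed, or takes place within consultations that would happen anyway, D + C approaches 0 and the ratio approaches 1.

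The illustrations thus run from about 1 to 3.17 according to what is assumed. They show how the answer depends on the inputs and do not estimate the shortfall.

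**The case against.** The strongest reply is that the costing section is consistent within itself. Its label, its input and its stated use all refer to medication review, so the mismatch may lie only in the word used in the aim. That is fair, and it is why relabelling is an acceptable fallback. It does not remove the mismatch: the aim promises a cost of the intervention, and no stated rule delivers one.

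A second reply is that review time may already include feedback to the physician, because component 1 is defined as the review with feedback and recommendation. This stands. A reader might infer that discussion is certainly left out of the costing, but the article does not draw the boundary of review time. The reply does not reach communication with other prescribers, which is a separate component with its own count.

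Third, the list of process data is introduced as examples, and a condensed article may leave the details of staff-time capture to the full protocol. One therefore cannot say that these activities will not be timed. The point rests on the costing rule, which the article does state and which names review time alone.

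Fourth, a reader might infer that the savings side credits both components while the cost side prices one, so that the whole comparison favours the intervention. The documents do not support this. Medication data are taken at the review and retrospectively from the last geriatric clinic appointment, and communication to other prescribers follows the change. No later collection is described in which other prescribers' responses would appear as savings. The savings side also counts only medication costs and leaves out consequences named in the Introduction, such as adverse drug reactions, falls and hospitalisation. The direction of bias is clear for the manpower term. It is not established for the economic balance as a whole.

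Finally, this is a secondary analysis that the article calls basic, in a feasibility study of 30 patients per site, and the article ties no cost threshold to it. That limits the stakes, but a basic analysis should still cover what its aim names.

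**Conclusion.** The concern holds in a limited form. Under the stated rule, physician communication with other prescribers is not costed, and neither is physician-pharmacist discussion unless it falls within review time. Manpower cost for the intervention is therefore understated, provided these steps take some staff time beyond usual care. This direction does not depend on physicians being paid more per minute than pharmacists.

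The size cannot be derived from the documents. A reader might take a figure such as 1.8 to 3.2 times the planned cost from the illustration. That range rests wholly on assumed durations and an assumed wage ratio, and it treats all discussion as outside review time, charges communication to every patient, and counts none of the time as usual care. It should not be quoted as a finding.

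**What to change.** In Secondary outcomes and data collection, define manpower cost per patient as the sum of:

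1. pharmacist review time, stating whether it includes feedback to and discussion with the physician;
2. physician and pharmacist discussion time not already counted in item 1, limited to time beyond usual care;
3. physician documentation and communication time, also limited to time beyond usual care.

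Price each at the wage rate of the staff member who does the work. For items 2 and 3, multiply the planned counts of discussions and communication efforts by a stated low and high duration per event, or by durations from a brief timing sample; include documentation time in the duration set for each communication effort. Report the result as a sensitivity range around the review-only figure.

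If this is not feasible, label the result as the cost of the medication review, not of the intervention, and reword the aim to match.

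The cost is a few sentences of text, a little extra analysis and, if chosen, a short timing exercise. No patient procedure changes. The drawback for the study team is a less favourable manpower figure.

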As our intervention was developed with the considerations on integrating medication review into routine outpatient care, variations in the delivery format between the sites were accommodated, due to the operational context and preference in practice at each site. For instance, there are two modes of recruiting eligible patients at both sites. One site has the option of calling patients beforehand to introduce the study, whereas the other site will mainly recruit patients on-the-spot during the day of appointment. Patients who consent to participate in the study will undergo a one-time medication review with a pharmacist. Medication review will be conducted either in-person or through a tele-med consultation, using preferred prescribing tools of choice (e.g., Beers criteria, STOPP/START) by the site pharmacists. Findings of any PIMs and other issues will be highlighted to the physicians so that they could take this information into consideration when making prescribing decisions during their consultations with patients. The changes would then be documented and communicated to the patients and other relevant prescribers via discussions or a memo. The feasibility of implementing medication reviews in routine outpatient practice among the stakeholders (patients, physicians, pharmacists) will be evaluated through surveys. In addition, in-depth interviews will also be conducted with selected implementers (physicians and pharmacists) to understand additional barriers experienced in the implementation process.

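### The drug-cost saving is built from stopped and substituted medicines and does not name those started or increased after the review, so this omission can only push the reported saving upward

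*Protocol article*

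**What the plan says.** The protocol article lists a cost analysis as a secondary aim. Under Study aims and objectives it is to be "based on manpower cost and the cost of PIMs and/or medications with other issues identified before and after the medication reviews".

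Under Secondary outcomes and data collection, the general sentence says the analysis will "compare the cost of manpower for medication review and the cost of PIMs or other medications issues identified before and after the medication reviews". Two more specific sentences follow. For staff cost: "Manpower cost to conduct medication reviews will be estimated by the time needed to a conduct a medication review". For drugs, the cost of issues identified and resolved is collected "to estimate the monthly cost savings from discontinued medications and any substituted medications". Medicines are priced at the private, pre-subsidy unit cost. The result is to inform whether medication review can be sustained in routine care over the longer term.

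Under Intervention specification, each patient "will undergo a one-time medication review with a pharmacist", carried out "using preferred prescribing tools of choice (e.g., Beers criteria, STOPP/START) by the site pharmacists". The Introduction expands START as a tool that alerts to right treatment. The pharmacist reports PIMs and other issues to the physician, and the resulting changes are documented and communicated.

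**The concern.** The sentence that defines the drug-cost result names two kinds of change, stopping and substituting. A review that may use START, and that looks at issues other than PIMs, can also lead to a medicine being started or a dose being raised. Those changes cost money every month, just as a stopped medicine saves it. If only the named changes are costed, the result is a gross saving that will be read as the effect of the review on drug cost.

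The cost analysis is one of the inputs that the Discussion lists for planning the scale-up study. A gross saving reported as if it were net would make the review look cheaper to sustain than it is. Because the choice of tool is left to each site's pharmacists, the understatement could also differ between the two sites and blur a comparison of them.

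**Working it through.** The document states no cost, saving or time horizon, so there is no figure to reproduce. The check is a reading of the text, followed by an accounting identity whose values are all assumptions.

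**Reading the text**

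| Type of change after review | Named in the saving sentence? | Covered by the broader before/after wording? |
|---|---|---|
| Stopped | Yes | Yes |
| Substituted | Yes | Yes |
| Dose increased on a flagged medicine | No | Possibly |
| Newly started | No | Not clearly: it has no entry before the review as a PIM or problem medicine |

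The broader wording is that of the aim and of the general cost sentence. It narrows the gap for dose increases but does not clearly close it for new medicines.

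**Direction**

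Let S be the monthly saving from stopped and substituted medicines, A the monthly cost of medicines started or increased, C the one-time manpower cost and m the number of months, all per patient.

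- Drug-cost result as written: S per month
- Net drug-cost result: S − A per month
- Difference: S − (S − A) = A, which is never negative

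So leaving A out can only overstate the saving, and by exactly A. The documents give no value for A.

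**What it could do (assumed values, arbitrary currency)**

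Net position after m months = m × (S − A) − C, with break-even at m = C / (S − A). Take C = 30 and S = 20.

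| A | S − A | Break-even (months) |
|---|---|---|
| 0 (as written) | 20 | 30 / 20 = 1.5 |
| 5 (25% of S) | 15 | 30 / 15 = 2.0 |
| 10 (50% of S) | 10 | 30 / 10 = 3.0 |
| 20 (100% of S) | 0 | never |

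**Does the sign change?**

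Assume 0.5 medicines stopped per patient at 10 units a month, so S = 0.5 × 10 = 5.

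- Started medicines also at 10 units: 0.2 started gives 5 − 0.2 × 10 = +3; 0.5 started gives 5 − 0.5 × 10 = 0. No reversal.
- Started medicines at 30 units, 0.5 started: 5 − 0.5 × 30 = −10. Reversal.
- With 0.2 started, reversal needs a price above 5 / 0.2 = 25 units.

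With these counts, a reversal therefore rests on assuming that started medicines cost more than stopped ones, which nothing in the document supports or excludes.

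**Time base**

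With A = 0, C = 30 and S = 20, the net position is 1 × 20 − 30 = −10 at one month, 6 × 20 − 30 = +90 at six and 12 × 20 − 30 = +210 at twelve. The answer depends on the horizon, but not in a fixed direction.

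**The case against.** The strongest reply is that the gap is read from silence. The saving sentence does not say that only these changes count and excludes nothing. The aim and the general cost sentence are wider, other medication issues is not defined, and the sentence cites a source for its method that is not at hand. This stands in part: the document does not expressly exclude started or increased medicines, and a dose increase on a flagged medicine may be covered. But the sentence that specifies the calculation is narrower than the aim, and a newly started medicine is not clearly caught by either.

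Three stronger readings are tempting, and the document does not support them.

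- A reader might infer that setting a monthly saving against a one-time review makes the analysis one-sided. It does not. Over one month the mismatch works against the intervention; an assumed long persistence of the changes works for it. The missing horizon leaves the comparison undefined, and an article may leave that detail to the full protocol.
- A reader might take "Ensuring proper documentation on reasons behind addition or removal of medications" in Table 1 as proof that Pro-M adds medicines. Those words stand in the column on the phase 1 context. The Pro-M column for that row speaks of documenting indications and communicating changes. What makes additions possible is START, one of several example tools, and their frequency is unknown.
- A reader might infer that a reported saving would hide a true increase in cost. That needs prices that the document does not give.

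It is also fair to say that the stakes are modest: a basic cost analysis, a secondary aim, 30 patients per site at two sites, and no decision rule tied to the saving.

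**Conclusion.** The point holds in a limited form. The drug-cost result is specified from stopped and substituted medicines, while the permitted tools and the scope of the review allow medicines to be started or increased. Leaving those out overstates the saving by their monthly cost. That amount cannot be estimated from the document; it is zero if no medicine is started or increased, and the break-even figures above only illustrate the mechanism.

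The conclusion rests on two assumptions: that the specific sentence, rather than the broader aim, governs the calculation, and that at least some reviews lead to a medicine being started or increased. The upward direction applies to this omission. Dose reductions are not named either, and leaving those out would act the other way, which is a further reason to cost all changes. The horizon is a matter for clarification and adds nothing to the case for bias.

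**What to change.** Replace the saving sentence with wording to this effect: the drug-cost result is the net change in monthly drug cost per patient over all documented changes that follow from the review (stopped, substituted, started, dose changed), every medicine priced at the same private, pre-subsidy unit cost; saving and added cost are reported separately as well as net.

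As a secondary clarification, state the horizon over which the net monthly change is set against the one-time manpower cost, for example as months to break even.

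The cost is small. Changes are already to be documented, so most of the work is pricing some further medicines. Some extra recording may be needed: the article describes collecting data on PIMs and other issues identified, and does not say that complete medication lists before and after the consultation are held. The reported saving may look less favourable.
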